### Objectives

The present study was developed to better understand the effects of personalizing rehabilitative treatments for patients with persistent concussion symptoms. Our primary aim is to evaluate the effectiveness of a personalized rehabilitation program based on subgroup classification, as measured by The Rivermead Post-concussion Symptoms Questionnaire (RPQ) when compared to an active control. Specifically, the objective is to assess whether personalizing rehabilitation following a standardized examination affords improved recovery when compared to an active control, which is reflective of the current standard of care for this population. Given symptoms are non-specific, we hypothesize that participants undergoing a personalized rehabilitation program derived from subgroup classification following a standardized exam will demonstrate clinically meaningful and statistically significant improved Rivermead Postconcussion Questionnaire scores when compared to the active control whose therapy approach is based on general rehabilitation recommendations.

Our secondary aim is to examine participants’ cognition Pre and Post-treatment (6 and 12-week follow-up points) via a quantitative electroencephalogram (EEG). Due to the various ostensible drivers of impaired cognition in this population, such as neck pain, sleep impairment, and altered mood, the EEG will serve as an objective cognitive evaluation.

Our tertiary aim is to examine at baseline and the follow-up points, participants’ Neck Disability Index, Patient Health Questionnaire (PHQ-9) and electrophysiological brain activity changes as measured by quantitative EEG. These outcomes will be compared to the standardized clinical examination findings as well as the RPQ. This will be done to identify any possible neuro-biomarker (abnormal ERPs), level of perceived neck disability or baseline level of depression that is predictive of treatment responders versus non-responders.

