### Personalized care program

On the first therapy session, participants in the personalized care stream will be provided reassurance and psychoeducation via the bio-psycho-social model on understanding persistent symptoms consistent with usual care. Additionally, they will be afforded up to 12 treatments over the course of 6 weeks. The time frame of 6 weeks was selected given the treatment structure of prior clinical trials examining the effectiveness of physical interventions to address physical symptoms such as headaches, dizziness and neck pain [29]. Treatments will be standardized; however, given the heterogeneity of symptoms, components of the treatments will be personalized to the participants based on what subgroup they’re classified into at baseline. Personalized rehabilitative care differentiated by subgroups is outlined below:

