**Autonomic group -** Participants will receive 60 min twice per week of supervised progressive sub-symptom aerobic exercise, as well as mindfulness-based training. As previously indicated, the target heart rate will be determined by the BCTT. This test will be done weekly to ensure the timely advancement of the target heart rate while participants’ rehabilitation and recovery progress. Participants will be instructed on various mindfulness-based techniques they can perform at home; however, in the clinic twice per week, a box-breathing technique will be utilized. Participants will be instructed to perform a minimum of 20 min of sub-symptom aerobic exercise as well as 20 min of mindfulness-based training daily outside the supervised exercise sessions.**Cervical group -** Participants will receive bi-weekly physical therapy to the cervical spine. Physical therapy will include soft tissue therapy directed to the cervical myofascial tissues and graded cervical spine facet mobilizations. Participants will also receive supervised 20 min of progressive neck isotonic strengthening exercises. Additionally, participants will be instructed to also perform daily 20 min of general neck stretches, range of motion exercises and neck strengthening exercises outside the supervised exercise sessions.**Vestibulo-Ocular group -** Patients will receive bi-weekly individualized oculomotor, vestibular and balance exercises including adaptation exercises, gaze stability exercises, visual-vestibular integration exercises, habituation exercises, and static and dynamic balance exercises. They will also be instructed to perform daily 20 min of individualized vestibular and oculomotor exercises based on their clinical exam outside the supervised exercise sessions.

In cases where participants are classified into more than one subgroup, they will receive the listed treatments provided to the sub-groups they are classified under. However, the frequency (twice per week) and duration (6-weeks) of care will not change regardless of subgroup determination.

Lastly, participants will be asked to refrain from seeking additional therapy; however, should they choose to undertake additional therapy outside of the trial they will be asked to document the modality and frequency of said therapy in the provided treatment adherence calendar that every participant receives at the start of the trial.

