### Active control (usual care program)

All participants in the active control group will receive ‘usual care’, (one-hour session once a week for 6 weeks). The usual care model will consist of a single-hour session, provided at the first visit following the baseline assessment, devoted to reassurance and psychoeducation via the bio-psycho-social model on understanding persistent symptoms, including advice on adaptive illness behaviours, such as gradually resuming premorbid activities and avoiding excessive rest and “all-or-nothing behaviour”. Continuing, they will be educated on the fact that symptoms can be exacerbated not only with physical activity but also with extended cognitive load, which occurs commonly during working hours and social situations. As such they will be informed to take 5-10-minute breaks every hour if working and to find quiet spaces during busy social situations periodically. Additionally, as part of their weekly one-hour therapy sessions, participants will be afforded 30 min supervised symptom-limited aerobic exercise sessions. They will also be instructed to perform 20 min of symptom-limited aerobic exercise daily outside the supervised exercise sessions. Symptom-limited exercise will be defined as any form of aerobic exercise the participants will be able to perform without causing a greater than 2-point change in total symptoms as rated on an 11-point pain numerical rating scale (0–10) during their training. They will be instructed to rate their symptoms at rest before the exercise period and then exercise aerobically for 20 min without worsening their symptoms. They will be instructed to stop exercising and rest should their baseline resting symptoms exceed a 2-point increase during the exercise session. Additionally, when clinically indicated based on the standardized exam, participants will receive 20 min of general neck active range of motion exercises and stretching along with 20 min of generalized static and balance exercises. Participants will be advised to perform the neck and balance exercises two to three times per week outside of the supervised exercise sessions.

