## Discussion

The results of the project may have implications for helping to establish real-world personalized treatment protocols for the rehabilitation of persistent concussive symptoms. Currently, single-therapy trials make up the vast majority of studies examining the efficacy of treatments on recovery from persistent concussion symptoms. Additionally, to date, the few trials examining the effects of sub-symptom aerobic exercise have only been compared to a full-body stretching program [43, 44]. Given the consistently positive responses that exercise seemingly affords this population [8, 9], it is imperative to continue to evaluate optimal parameters. This is especially important because of the well-documented high degree of so-called stubborn exercise responders. The literature has consistently shown that should aerobic training volume and or intensity not be sufficiently intense for the individual, then no observable adaptions will occur [45]. In the present trial, both treatment programs afford participants active rehabilitation, with a focus on aerobic exercise training.

We hope to demonstrate that a personalized rehabilitative treatment protocol, which targets specific symptoms from the global concussion umbrella will lead to superior outcomes. Additionally, we hope that through the undertaking of the trial, we identify potential biomarkers, as measured by EEG and the standardized physical assessment, that can be predictive of response to therapy. Finally, we hope to positively contribute to the body of knowledge supporting therapies to treat impairments in post-concussive patients, which have been labelled as permanent.

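### The trial can compare a personalised programme with usual care, but not isolate personalisation: supervised sessions differ up to twofold, and the article disagrees with itself on aerobic content

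*Protocol article*

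**What the plan says.** All references are to the protocol article.

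- **Objectives.** The primary aim is at programme level: "Our primary aim is to evaluate the effectiveness of a personalized rehabilitation program based on subgroup classification". The sentence that follows narrows it to tailoring itself: "the objective is to assess whether personalizing rehabilitation following a standardized examination affords improved recovery when compared to an active control".
- **Personalized care program.** Participants are told that "they will be afforded up to 12 treatments over the course of 6 weeks", and "the frequency (twice per week) and duration (6-weeks) of care will not change regardless of subgroup determination". Aerobic exercise is listed only for the autonomic subgroup. For the cervical subgroup the text reads "Participants will receive bi-weekly physical therapy to the cervical spine", followed by neck strengthening and home neck exercises. The vestibulo-ocular subgroup receives oculomotor, vestibular and balance exercises. Neither of these two lists contains aerobic exercise, supervised or at home.
- **Active control (usual care program).** The schedule is "one-hour session once a week for 6 weeks". All control participants have 30 minutes of supervised aerobic exercise in the weekly sessions and 20 minutes daily at home. In addition, "when clinically indicated based on the standardized exam, participants will receive 20 min of general neck active range of motion exercises", together with balance exercises.
- **Discussion.** The summary of the two arms is that "both treatment programs afford participants active rehabilitation, with a focus on aerobic exercise training".

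**The concern.** Two things do not fit together.

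First, the objective sentence names personalising as the thing tested, but number of supervised sessions goes with arm. Whoever receives the personalised programme is also offered up to twice as many visits. The article says that participants could not be adequately blinded (Randomization and masking), and the primary outcome is rated by the patient (Primary outcome). Extra clinician contact is therefore a plausible rival explanation for a benefit. The control is not free of examination-guided content either, so the contrast is not simply tailored against untailored.

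Second, a reader of the Discussion would take aerobic exercise to be common to both arms. The intervention section does not bear this out for part of the population. The point matters on the article's own reasoning: the Background treats aerobic exercise as a mainstay of care, and the Discussion argues that too little training volume or intensity produces no adaptation.

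At stake is what the trial may conclude. A positive result could be reported as evidence for personalisation when it supports only the package.

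**Working it through.** **Supervised sessions over 6 weeks**

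- Personalised arm: 2 per week × 6 weeks = 12. This reproduces the stated maximum of 12. The article fixes the frequency at twice per week for every subgroup, which also settles how its term bi-weekly is to be read.
- Control arm: 1 per week × 6 weeks = 6.
- Ratio: 12 / 6 = 2.0, as a maximum, because 12 is an upper limit.

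In minutes, the comparison is possible only where a session length is given. For the autonomic subgroup it is up to 12 × 60 = 720, against 6 × 60 = 360 in control. No total session length is given for the cervical or vestibulo-ocular subgroups.

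**Does the crossover help?** No. Each participant receives both programmes, but the session count travels with the programme in both periods. The crossover does not separate contact from tailoring.

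**Aerobic exercise as written, over 6 weeks (42 days)**

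| Group | Supervised min | Home min | Total |
|---|---|---|---|
| Control, all participants | 30 × 6 = 180, or 30 × 5 = 150 if the first visit is education only | 20 × 42 = 840 | 990 to 1020 |
| Personalised, autonomic | up to 60 × 12 = 720, if the full hour is aerobic | 20 × 42 = 840 | up to 1560 |
| Personalised, cervical and/or vestibulo-ocular only | none listed | none listed | 0 listed |

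For autonomic participants the personalised arm has up to 720 / 180 = 4.0 to 720 / 150 = 4.8 times the supervised aerobic minutes of control. For those without an autonomic classification it has none listed, against 150 to 180 in control. The aerobic contrast thus points in opposite directions by subgroup.

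**Who is affected?** The Inclusion criteria admit a participant on any one of the three subgroups, so people without an autonomic classification are eligible. Anyone classified as autonomic plus another subgroup receives the treatments of both and so does get aerobic exercise. The conflict with the Discussion is confined to the cervical-only, vestibulo-ocular-only and combined cervical and vestibulo-ocular participants.

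**The case against.** The strongest reply is that the trial is pragmatic and mostly says so. The title, the closing paragraph of the abstract, the primary aim and the hypothesis all compare a programme with usual care or an active control. Unequal contact is then part of the package, and both schedules are openly stated. This stands. It means that one sentence of the Objectives needs changing, not the design, and that the hypothesis can stay at programme level.

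A second reply is that different content by subgroup is what personalisation means. The article ascribes symptoms to other causes when a patient tolerates exertion, so leaving aerobic work out of two subgroup lists may be intended. This also stands: differing content is not in itself a flaw. It does not rescue the Discussion sentence, which describes both programmes as focused on aerobic exercise.

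A third reply is that the control's examination-guided exercises are general, while the personalised ones are specific. That is fair. The contrast in tailoring is blurred, not erased.

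Some stronger readings are tempting and are not supported:

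- A reader might infer that any conclusion about personalisation would be wrong. The documents show only that it would be unsupported, because rival explanations are open.
- A reader might infer that a null result would come from opposing aerobic contrasts cancelling out. That depends on the subgroup mix and on effects by subgroup, and the article gives neither.
- A reader might apply 720 against 360 contact minutes to the whole trial. Sixty minutes is stated only for the autonomic subgroup and the control.

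**Conclusion.** The point holds in a limited form. With up to 12 supervised sessions against 6, and some examination-guided exercise in the control, the design cannot attribute a difference to personalisation as distinct from contact and content. The comparison of the personalised programme with usual care is unaffected and remains answerable in principle.

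The Discussion also conflicts with the intervention section on aerobic exercise for participants without an autonomic classification: none is listed in the personalised arm, against about 150 to 180 supervised minutes in control plus 20 minutes daily at home.

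These figures assume that sessions are delivered as scheduled and that what the article does not list is not given. The lower control figure assumes an education-only first visit. The 720-minute autonomic figure is an upper limit.

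**What to change.** 1. In the Objectives, reword the sentence on whether personalising improves recovery to match the primary aim: a personalised programme with up to twice the supervised sessions, compared with usual care.
2. Limit the reported conclusion to that package contrast, and do not present the trial as a test of personalisation itself.
3. Reconcile the Discussion statement on aerobic exercise with the two intervention sections. This review takes no position on which content is right.

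Two additions are optional and would normally sit in the analysis plan: attended sessions by arm, and an exploratory estimate of the effect by baseline autonomic classification. With 50 participants the latter would be low-powered, and neither would separate contact from tailoring.

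The cost is wording and a narrower claim. The required changes need no new data and no change to the design.

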## Methods

### Ethics approval

Ethics approval for this clinical trial has been granted by the University Health Network Research Ethics Board (#22-5560). All participants are required to provide both verbal and written informed consent before commencing any experimental procedures. [protocol version 4, January 13, 2023]

### Study design

We will be conducting a 12-week case-crossover randomized controlled trial (see Table 1). At baseline, following the standardized examination, completion of the primary outcome measure (RPQ), baseline quantitative EEG and secondary outcome measures (NDI and PHQ-9), participants will be randomized to either Group A: a personalized care program followed by an active control or Group B: an active control followed by a personalized care program. No washout period will be used between interventions. It was assumed that given both interventional groups have a focus on rehabilitative therapy that no wash-out period was needed. Participants will undergo 6 weeks of care in their respective streams. After 6 weeks, participants will undergo a re-examination. They will then crossover and undertake the alternative treatment for 6 weeks. At the end of 12 weeks, participants will undertake the endpoint examinations.

**Table 1 Tab1:** Enrolment schedule, interventions and assessments

	Study Period						
	Enrolment/Baseline assessment	Allocation	T1	Mid-point assessment (6 weeks)	Cross-over	T2	End-point assessment (12 weeks)
**TIMEPOINT**							
**Eligibility**	X	X					
**Informed consent**	X						
**INTERVENTIONS**							
**Personalized care program**			X	X	X	X	X
**Usual care program**			X	X	X	X	X
**ASSESSMENTS**							
**RPQ-3**	X			X			X
**RPQ-13**	X			X			X
**NDI**	X			X			X
**PHQ-9**	X			X			X
**EEG**	X			X			X

T1: \First 6 weeks of rehabilitation; T2: Second 6 weeks of rehabilitation; RPQ: Rivermead Postconcussion Questionnaire; NDI: Neck Disability Index; PHQ-9: Patient Health Questionnaire; EEG: Electroencephalography via NeuroCatch platform

### Population

Participants will be recruited from external community concussion clinics around the greater Toronto area as well as by internal advertisement at the University Health Network. Internal advertisements will consist of posters posted at the University Health Network. Recruitment via external community clinics will be a result of referrals by physicians working with patients who are suffering persistent concussion symptoms. Participants will undergo therapy at either the KITE Innovations and Rehabilitation Clinics located within the Toronto Rehabilitation Institute, Toronto, Ontario, Canada or the Pain and Wellness Centre, an interdisciplinary pain management clinic located just north of the city of Toronto, Ontario, Canada.

### Inclusion criteria

21-years and older.Meet the definition of postconcussion syndrome as defined by Tator et al. (2016), which requires a participant to report any 3 symptoms or more (from an inclusive list of the 40 most commonly reported persisting symptoms) lasting at least 1-month following the diagnosis of a concussion [13]. Concussion was defined according to the 6th International Consensus Statement on Concussion in Sport [10].Have adequate language skills in English to read and take part in rehabilitation treatment programs.Demonstrate an objective impairment on the baseline standardized exam, placing the participant into one of the three subgroups (autonomic, cervical or vestibulo-ocular).

### Exclusion criteria

In-patients at Toronto Rehabilitation Institute or any other affiliated University Health Network clinics.Participants will be excluded should their clinical examination be unremarkable for any positive physical findings and therefore their dominant symptomatology places them into the Affective / Cognition subgroup described by Leddy et al. [7].Have a chronic infectious disease.Uncontrolled hypertension.Other neurological disorders (not attributed to their primary diagnosis).Cancer treatment (other than basal cell carcinoma), craniotomy, or refractory subdural hematoma.long-term use of psychoactive medications that would compromise their ability to comprehend and perform study activities.Those with pacemakers or elevated cardiovascular risk.Ongoing litigation surrounding their injury.Have been diagnosed with a moderate or severe brain injury prior to enrollment, or their post-concussive symptoms have persisted beyond 12 months.

### Randomization and masking

We will use simple randomization to allocate participants to one of two sequences of interventions: Group A: personalized care program followed by active control; or Group B: active control followed by personalized care program. The study coordinator (NM) conducted the randomization using a randomized table generator (GraphPad Software Inc, La Jolla, CA). Randomization will be concealed; no other study personnel will be aware of the intervention assignments. However, it was not possible to blind the study coordinator (NM) as they are one of the main treating clinicians. Additionally, it was not possible to ensure adequate blinding of the participants, given the necessary thorough description of the treatment procedures that occurred during the informed consent process.

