**Methods:**

We will conduct a multi-center 12-week case-crossover randomized controlled trial. 50 participants will be recruited from out-patient University Health Network clinics and community-based clinical practices around the greater Toronto area. Participants will be randomized at baseline to Group A: a personalized care program followed by an active control or Group B: an active control followed by a personalized care program. Participants will be included should they be 21 years of age and older and have symptoms that have persisted beyond 4 weeks but less than 1 year. Participants will undergo 6-weeks of care in their respective streams. After 6-weeks, participants will undergo a re-examination. They will then crossover and undertake the alternative treatment for 6 weeks. At the end of 12 weeks, participants will undertake the endpoint examinations. The primary outcome will be the Rivermead Postconcussion Questionnaire (RPQ). The secondary outcomes will be changes in standardized clinical examination, Neck Disability Index (NDI), Patient Health Questionnaire (PHQ-9) and an electroencephalography (EEG) via NeuroCatch^™^. The statistical analysis to be performed is composed of an adjusted model using an analysis of variance, specifically using an unpaired t-test to test for associations between variables and outcomes.

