### Intervention

The study coordinator (NM) will perform all components of the listed assessments/procedures. The interventions will be delivered by advanced-trained chiropractors at the Pain and Wellness Centre and the study coordinator (NM) at the KITE Innovations and Rehabilitation Clinics.

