### Statistical analysis

The primary outcome is a change in symptoms following rehabilitative interventions using the RPQ. Previous research examining the internal construct validity of the Rivermead Post-Concussion Symptom Questionnaire suggested that a score of 2 or more on at least 3 of the 16 symptoms represents an unfavourable outcome [40]. We chose to calculate the study sample size by assuming an effect size. Unfortunately, to date, no validated change scores exist, thus we prescribed a cut-off of 15% improvement as minimal clinically importance difference (MCID). This translates into a change of 2 points on the RPQ-3 and a change of 8 points on the RPQ-13. This agrees with prior clinical literature examining changes post-intervention on concussion symptoms [41]. Based on this effect size, a power of 80%, a significance level at *p* < 0.05 and a two-sided t-test, we calculated that a sample size of 50 participants was necessary [42].

Descriptive statistics will be applied to all outcome measures to assist in summarizing the results. Participant demographic data will be compared to assess compatibility between groups, specifically before the crossover point.

The statistical analysis conducted in this research is composed of an adjusted model using an analysis of variance to test for associations between variables and outcomes (two groups [personalized care or usual care] x 3 times [baseline, week 6 and 12]) [42]. The statistical analysis conducted in this study will be made using SAS OnDemand for Academics 2021. The data set is composed of six variables, two independent variables –personalized care group or usual care group – and four dependent variables – age, sex, and result of treatment on the RPQ graded as total score and sub-classification (RPQ-3 and RPQ-13). A 2-way analysis of covariance (ANCOVA) (two groups [personalized care or usual care] x 3 times [baseline, week 6 and 12] x baseline secondary outcomes [ERPs, NDI and PHQ-9] will be used to examine the effects of the rehabilitation programs while controlling for these covariates. Lastly, an unpaired t-test will be used to assess the effects of the rehabilitation programs on the secondary outcomes. In addition to the per-protocol analysis, an intention-to-treat analysis will be conducted.

All unintended effects, harms and/or dropouts during the program will be recorded.

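### Simple randomisation of 50 people leaves site and baseline subgroup to chance, and the stated model adjusts for neither; the cost is precision and credibility, not validity

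*Protocol article*

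**What the plan says.** **Allocation.** Randomization and masking states: "We will use simple randomization to allocate participants to one of two sequences of interventions". No block, stratum or minimisation factor is named. The study coordinator, who is also one of the main treating clinicians, runs the randomisation. That section uses both the future and the past tense, so it is unclear whether the list already exists.

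**Size.** Under Statistical analysis: "we calculated that a sample size of 50 participants was necessary".

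**Sites and staff.** Population names two places of treatment: "Participants will undergo therapy at either the KITE Innovations and Rehabilitation Clinics", or a community pain clinic. Intervention ties staff to site: "The interventions will be delivered by advanced-trained chiropractors at the Pain and Wellness Centre", and the study coordinator treats at the other site.

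**Subgroup.** Inclusion criteria require an impairment that places the person in an autonomic, cervical or vestibulo-ocular subgroup. Personalized care program makes the content of treatment depend on that subgroup and allows membership of more than one. Study design places randomisation after the standardised examination, so subgroup is known by then.

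**Model.** Statistical analysis gives a group-by-time ANOVA on the RPQ (baseline, week 6, week 12), an ANCOVA adding baseline ERPs, NDI and PHQ-9, and an unpaired t-test for secondary outcomes. Age and sex are listed in the data set, although they are labelled as dependent variables. Site and subgroup are not named. A comparison of demographics between groups is planned, specifically before the crossover.

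**The concern.** With 50 people and unrestricted allocation, the two sequences can easily differ in the share treated at each site or in the mix of subgroups. These are not incidental variables: the protocol makes one decide who delivers treatment and the other decide what personalised treatment is. If recovery differs by site or subgroup, an uneven mix moves the observed between-group difference in RPQ, and the covariates named would not take that out. Baseline NDI may partly stand in for the cervical subgroup (an inference), but nothing listed stands in for site.

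The comparison most exposed is the one between sequences at week 6. There is no washout, so it is the only comparison that carryover cannot touch. It is also the only one without a second period to offset chance differences between people.

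**Working it through.** **1. The plan's own figure.** Inputs from Statistical analysis: 80% power, alpha 0.05, a two-sided t-test and a total of 50. No SD or standardised effect is given, so 50 cannot be derived from the stated inputs alone. Assuming d = 0.80, the normal formula is n per arm = 2(1.960 + 0.842)²/d² = 15.70/0.64 = 24.5, so 25 per arm and 50 in total. The t-based version gives 52. So 50 fits an independent-groups test at d of about 0.8. A paired test on 50 people would detect d of about 0.40. The calculation therefore reads as a between-group one.

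**2. Arm sizes.** Equal allocation is assumed, since the ratio is not stated. Tails are from Binomial(50, 0.5). Power is from the noncentral t at d = 0.809, which gives 80% at 25:25.

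| Split or worse | Probability | Power at that split |
|---|---|---|
| 28:22 | 48.0% | 79.4% |
| 30:20 | 20.3% | 78.4% |
| 32:18 | 6.5% | 76.7% |

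Unequal arm size alone matters little.

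**3. Site and subgroup mix.** The article gives no frequencies, so these are assumptions: site split 50:50, 70:30 or 80:20; subgroups equal and exclusive, 50/30/20 and exclusive, or overlapping independently at 50% each or at 60/70/50%. Each scenario was simulated with 40,000 simple randomisations. An event is an absolute difference between sequences in the share at a site, or in any one of the three subgroups, of at least the threshold.

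| Threshold (percentage points) | Site or any subgroup, range over scenarios |
|---|---|
| 10 | 83–93% |
| 15 | 58–77% |
| 20 | 34–53% |
| 25 | 16–28% |
| 30 | 6–14% |

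At 20 points, site alone accounts for 8–17% and any subgroup for 28–43%.

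**4. Effect on the test.** With site and subgroup effects of 0.5 to 0.8 SD, the type I error of an unadjusted t-test under simple randomisation stays at 4.9–5.0%.

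**5. Possible shift in the estimate.** As an illustration only, suppose one subgroup recovers 8 points more on the RPQ-13 than the others. A 20-point imbalance in that subgroup shifts the arm difference by 0.20 × 8 = 1.6 points, and 1.6/8 = 20% of the stated 8-point MCID. The SD implied by step 1 is 8/0.809 = 9.9, so the standard error at 25:25 is 9.9 × √(2/25) = 2.8 points, and 1.6/2.8 = 0.57 standard errors.

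**6. What the remedies do.** By simulation, adding site and subgroup terms raises power from 67% to about 76% if their effects are 0.8 SD, and costs about 4 points if they are nil. Blocks of 4 (assumed size) stratified by site alone bring the chance of a 20-point site imbalance to zero, but leave the chance of a 20-point imbalance in some subgroup at about 33% (equal exclusive subgroups). Stratifying by site and subgroup removes both in simulation with exclusive subgroups. With overlap, however, there are 2³ − 1 = 7 subgroup patterns, hence 2 × 7 = 14 strata, or 50/14 = 3.6 people each, too few for blocks of 4 to fill reliably.

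**The case against.** **Simple randomisation is valid and clearly stated.** This stands. Step 4 shows that the error rate is unaffected, and an imbalance of the size in step 5 lies within the sampling variation that the confidence interval already carries.

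**A reader might infer that there is nearly an even chance of a material imbalance.** The documents do not support that as a fixed figure. They define no threshold for material and give no site split or subgroup frequencies. The probability runs from 6% to 93% as the threshold moves from 30 to 10 points. Nor can that probability be paired with the 1.6-point shift: the shift needs imbalance in the one subgroup that recovers differently, which happens in about 8–17% of trials at 20 points, and the 8-point subgroup effect is itself hypothetical.

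**Everyone receives both programmes.** A within-person contrast cancels stable site and subgroup differences. This also stands. It does not dispose of the point, because the stated analyses include between-group comparisons and an unpaired t-test, the sample size fits an independent-groups test, and the absence of a washout puts weight on week 6. A recovery rate that differs by site or subgroup is also not a stable difference.

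**Further covariates may sit in an analysis plan not shown.** Possible, but the article lists its model terms, and the objection is to that list.

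**Conclusion.** The point holds as a matter of efficiency and credibility. Allocation balances neither of the two factors that the protocol itself makes central, and the covariates named omit both. Under the assumed mixes, the chance of a difference of 20 points or more on site or at least one subgroup is about 34% to 53%. That range rests on the assumed frequencies, on the choice of 20 points, and on counting any one of four factors. It would be wrong to go further and call the test biased, the type I error inflated or the trial invalid. The weakness bears mainly on the week-6 between-sequence comparison and on any other unpaired comparison. It is worth correcting because the data needed are collected anyway.

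**What to change.** **Analysis (available whatever the stage of the trial).** Add site and baseline subgroup to the RPQ model as fixed terms. Enter subgroup as three yes/no indicators, because membership may overlap; if nobody overlaps, drop one indicator as redundant. Where the model is repeated-measures, include the interaction of each term with time, since it is differing recovery, not differing level, that would move a change from baseline. Cost: about four degrees of freedom, or roughly 4 points of power if neither factor is prognostic, with a gain if they are.

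**Allocation (only if it has not begun).** Use permuted blocks of randomly varied size, stratified by site. Leave subgroup to the model, because stratifying on overlapping subgroups would make the strata too small. This is worthwhile only if the list and block sizes can be kept from the treating coordinator, who now runs the randomisation. Someone independent would have to generate and hold the list, and that is the real cost. Without that separation, blocks in an open-label trial make the next assignment easier to predict, and the model change alone is preferable.

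**Text.** State whether the list has already been generated.
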